#### Secondary data collection: risk factors for the development of AIMSS

To investigate potential risk factors for the development of AIMSS, the following data will be collected: clinical, demographic, pathological and therapeutic variables; beliefs and perceptions in relation to hormone therapy will be assessed using the BMQ-AET (Beliefs about Medicines Questionnaire - Adjuvant Endocrine Therapy); and pain catastrophising will be measured using the Pain Catastrophising Scale.

### Data management

#### Quantitative data management

Quantitative data will be collected from several sources: medical records, Self-Report Questionnaires, PA logbooks (paper or email-based) and the results of paraclinical examinations.

They will be entered as they are collected, in each centre, either by authorised research professionals (investigator or team members listed in the delegation of tasks), directly into the electronic case report form, via their personal identifiers and in compliance with data protection regulations, or directly by the patients themselves via the secure Ennov Clinical platform (Ennov, Paris, France).

All data will be pseudonymised using a unique identification code. Automatic validation checks will be applied during data entry, and the sponsor’s clinical research unit will conduct regular monitoring. Any discrepancies or protocol deviations will be documented and communicated to investigators. The trial complies with International Council for Harmonisation Good Clinical Practice and applicable national data protection laws.

#### Qualitative data management

Two distinct semi-structured interview guides, one for patients and one for healthcare professionals, were developed based on the 14 domains of the TDF, following the methodology proposed by Cane *et al*.^25^ Each domain was explored through open-ended questions, supplemented by follow-up prompts as needed to elicit detailed responses.^24^

The guides were reviewed for content validity by two oncology healthcare professionals and a methodological expert to ensure their appropriateness for the target populations. Pilot testing was conducted with a patient partner and a healthcare professional, resulting in refinements to the clarity and wording of the interview items.

Interviews will be conducted at time point T2 by a doctoral candidate (NP) and a patient-researcher (AG), both of whom are trained in qualitative research methods. Each interview will last approximately 25–35 min and will be conducted in a single videoconferencing session. All participants will receive comprehensive written and verbal information about the study, including its objectives, interview procedures and data management protocols. With informed consent, interviews will be audio-recorded using a digital device, securely transferred to a password-protected computer and subsequently deleted from the recording device. Each interview will be transcribed verbatim and pseudonymised. NVivo V.15 software (QSR International) will be used to organise and analyse the data.

### Data analysis

#### Quantitative data analysis

The statistical analysis will be performed on the intention-to-treat population.

For the primary objective, the maximum intensity of musculoskeletal pain at 6 months (T2) will be compared between groups using parametric (eg, t-test) or non-parametric (eg, Wilcoxon-Mann-Whitney) tests, depending on data distribution.

Secondary objectives include evaluating the intervention’s effects on outcomes such as physical health, psychosocial well-being and treatment adherence. Analyses will include: (1) between-group comparisons at specific time points (T0, T1, T_APA_, T2), (2) between-group comparisons of change over time (eg, T0–T1, T1–T2) and (3) within-group longitudinal changes across time points.

Univariate and multivariate logistic regression models will explore factors associated with the occurrence of AIMSS. Qualitative variables will be compared using χ^2^ or Fisher’s exact test, as appropriate.

All analyses will be two-sided with a significance threshold of p<0.05. Missing data will be handled using appropriate statistical methods. Analyses will be conducted using R software (R Foundation for Statistical Computing, Vienna, Austria).

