### Study setting

This study will be conducted in two French hospitals: the gynaecological surgery departments of the Saint-Etienne University Hospital and the Lyon University Hospital (Hospices Civils de Lyon).

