### Assignment of interventions

Participants will be randomised using Ennov Clinical software. Randomisation will be stratified. The study centre will use a computer-generated pseudo-randomised list prepared in advance by a biostatistician. Given the behavioural nature of the intervention, blinding will not be possible.

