### Outcomes

#### Primary outcome

The primary outcome will be the score for the most intense musculoskeletal pain, assessed with the Nordic-style questionnaire, 6 months after the introduction of the AI (T2).

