#### Secondary outcomes: effectiveness aim

Secondary outcomes will evaluate the effects of the intervention on physical health and psychosocial well-being by assessing global pain, cognitive problems, physical condition, body composition and nutritional status, indicators of metabolic syndrome, heart rate variability, therapeutic adherence to the AI and adverse events related to the intervention. These outcomes will be assessed at four time points (T0, T1, T_APA_, T2) using validated questionnaires, clinical examinations and functional tests.

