.AIMSS, aromatase inhibitor-induced musculoskeletal symptoms; APA, adapted physical activity ; APN, Advanced Practice Nurse; BMI, body mass index; CG, control group; CRP, C-reactive protein; D, day; DLCO, diffusing capacity of the lung for carbon monoxide; EG, experimental group; FEV1, forced expiratory volume in 1 s; HOMA-IR, Homeostatic Model Assessment for Insulin Resistance; IV, inclusion visit; M, month; MWT, 6-minute walk test; PA, physical activity; PEF, peak expiratory flow; RV, residual volume; T0, pre-therapeutic phase; T1, initiation of the aromatase inhibitors; T2, 6 months after the initiation of the aromatase inhibitors; T_APA_, end of the 12-week APA programme; TLC, total lung capacity; VC, vital capacity; VO₂ max, maximal oxygen consumption; VO₂ peak, peak oxygen consumption; VT, tidal volume.

**Table 2 T2:** Summary of secondary outcomes and data collection methods for the effectiveness aim

Outcome domain	Outcome measure	Data collection	Assessment modality
**Global pain***	Musculoskeletal pain	Musculoskeletal pain intensity and localisation	Nordic-style questionnaire†
	Overall pain	Self-rated overall pain	Numerical Rating Scale†
	Quality of life	Quality of life score	FACT-B†, FACT-ES†
	Fatigue	Fatigue score	FACIT – Fatigue†
	Anxiety	Anxiety and depression scores	HADS†
**Cognitive function**		Perceived cognitive impairments	FACT-Cog†
**Physical condition**	Respiratory function	FEV1, PEF, VT, VC, RV, TLC, DLCO	Pulmonary function tests
	Cardiac function	VO₂ peak, VO₂ max, maximal heart rate, VO₂ at VT1, cardiac output at VT1, heart rate at VT1, blood pressure, oxygen saturation	Cardiopulmonary exercise test
	Cardiorespiratory endurance	Distance walked in 6 minutes	6-minute walk test
	Muscular strength	Isometric grip strength	Handgrip strength test
	PA level	Habitual levels of PA	Marshall questionnaire†, IPAQ†
**Body composition**	Anthropometric measurements	Body weight, height, body mass index, waist circumference and 4-site skinfold	Anthropometric assessment
	Malnutrition	MUST score	MUST†
**Evolution of a metabolic syndrome**		Waist circumference	Anthropometric assessment
		Blood pressure	Blood pressure measurement
		Lipid profile, assessment of insulin resistance and inflammatory status	Blood tests: lipid profile, HOMA-IR, C-reactive protein
**HRV‡**		HRV parameters	24-hour Holter ECG recording
**Therapeutic adherence to the AI**		Therapeutic adherence to the AI	Girerd self-assessment questionnaire†

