#### Initial assessment/randomisation (T0)

A clinical and paraclinical examination by the multidisciplinary sports medicine team during a day care hospital visit, before any therapeutic intervention, will include clinical data, cardiopulmonary exercise testing, pulmonary function testing, 24-hour Holter ECG monitoring, additional examinations and Self-Report Questionnaires. Patients will also be instructed on daily PA self-monitoring via an electronic or paper logbook. The estimated completion time is 2 min per day.

They will be randomised into two groups.

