### Sample size

#### Sample size for the primary outcome

The expected prevalence of AIMSS in the standard care group is approximately 40%. We hypothesise a 50% reduction (20%) in the experimental group with early implementation of APA.^20^ Considering an alpha risk of 5%, a power of 80% and a two-sided hypothesis, 82 patients per arm will be required. Assuming 10% unusable data, a total of 182 patients will be included.

Sample size for the qualitative component of the mixed-methods study (secondary implementation aim).

The principle of theoretical saturation will guide the sample sizes of the two groups (patients and healthcare professionals), once the collected data are sufficient to explain the phenomenon. Data collection, conducted progressively and in parallel with analysis, will define the final sample size.^21^

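### The primary comparison of T2 pain uses neither the T0 pain score nor the randomisation strata and leaves the test to the data: valid, but it gives up precision and leaves the effect measure open

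*Protocol article*

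**What the plan says.** The Primary outcome section defines the endpoint as a score at one time point: "The primary outcome will be the score for the most intense musculoskeletal pain, assessed with the Nordic-style questionnaire, 6 months after the introduction of the" aromatase inhibitor (AI). For that endpoint, Quantitative data analysis says that maximum pain intensity at T2 "will be compared between groups using parametric (eg, t-test) or non-parametric (eg, Wilcoxon-Mann-Whitney) tests, depending on data distribution". It names no covariate and no stratum. Change over time appears only under the secondary objectives, and multivariable modelling only for AIMSS risk factors.

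Elsewhere the article shows that baseline information exists. Table 2 lists the Nordic-style questionnaire as the source for "Musculoskeletal pain intensity and localisation". The secondary effectiveness section adds: "These outcomes will be assessed at four time points (T0, T1, T_APA_, T2) using validated questionnaires, clinical examinations and functional tests". Table 1 schedules the self-report questionnaires at T0. The T0 section places that visit "before any therapeutic intervention, will include clinical data", includes the questionnaires in it, and mentions allocation only after describing the assessments. Assignment of interventions states: "Randomisation will be stratified". It does not name the factors.

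**The concern.** A baseline value of the outcome, measured in everyone before allocation, is the natural covariate for the primary comparison. The eligibility criteria do not exclude women who already have musculoskeletal pain, apart from locomotor conditions that prevent cycling and absolute contraindications to physical activity. The endpoint is the worst musculoskeletal pain whatever its cause. Pain present at T0 can therefore carry through to T2 and add variability that the planned test leaves in the error term. Stratifying the randomisation and then leaving the strata out of the analysis tends to make the standard error too large if the strata predict pain.

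The choice of test is a separate matter. A t-test concerns a difference in means; Wilcoxon-Mann-Whitney concerns a rank contrast. Letting the distribution decide means that the effect to be estimated is not fixed in advance, in an open-label trial with a self-reported primary outcome. At stake are precision and a clearly defined result.

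**Working it through.** **1. The article's own figure.** Inputs from Sample size for the primary outcome: 40% v 20%, two-sided alpha 5%, power 80%. With the pooled two-proportion formula without continuity correction:

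n = [1.96·√(2·0.3·0.7) + 0.8416·√(0.4·0.6 + 0.2·0.8)]² / 0.20² = (1.2702 + 0.5323)² / 0.04 = 81.2, so 82 per arm.

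This matches the stated 82. The total also agrees: 164/0.9 = 182.2, stated as 182. These figures are for a comparison of proportions. The article gives no SD or target difference for the pain score, so it states no power for the test it plans.

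**2. A working effect size (assumption).** The standardised difference that gives an unadjusted two-sample test 80% power at 82 per arm is

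d = (1.96 + 0.8416)·√(2/82) = 2.8016 × 0.1562 = 0.4375.

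This is back-solved and is not a trial assumption.

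**3. Effect of adjusting for T0 pain.** With T0–T2 correlation ρ (not given in the article, so shown over a range), the variance of the adjusted contrast is (1 − ρ²) times the unadjusted variance. Equivalent unadjusted n per arm = 82/(1 − ρ²). Power = Φ(2.8016/√(1 − ρ²) − 1.96).

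| ρ (assumed) | Variance reduction | Equivalent n per arm | Power |
|---|---|---|---|
| 0 | 0% | 82 | 80.0% |
| 0.1 | 1% | 82.8 | 80.4% |
| 0.2 | 4% | 85.4 | 81.6% |
| 0.3 | 9% | 90.1 | 83.6% |
| 0.5 | 25% | 109.3 | 89.9% |
| 0.6 | 36% | 128.1 | 93.8% |

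Worked example for ρ = 0.5: 2.8016/√0.75 = 3.235; 3.235 − 1.96 = 1.275; Φ(1.275) = 0.899.

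**4. Does choosing the test by distribution inflate type I error?** Null trials were simulated with 82 per arm, 5,000 runs per scenario. A Shapiro-Wilk check at 5% was applied in each arm; the t-test was used if both arms passed and Wilcoxon otherwise. The rejection rate was 5.3% for normal data (5.2% for the t-test alone) and 4.8% for rounded scores bounded at 0 and 10. In the bounded scenario the check failed every time, so Wilcoxon was always used. The simulation standard error is about √(0.05·0.95/5000) = 0.3 points, so neither rate differs materially from 5%.

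**5. The strata.** The factors are not named and nothing is said about how strongly they predict pain, so no figure can be put on this loss.

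**The case against.** The strongest reply is that nothing here is an error. In a randomised trial the unadjusted comparison is unbiased and keeps its type I error, and its standard error already allows for chance imbalance at T0. That stands: the issue is efficiency.

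The gain may also be small. T0 comes 1 to 7 months before the AI starts, so 7 to 13 months before T2, with surgery and possibly chemotherapy and radiotherapy in between, and the pain of interest is caused by the AI. A reader might infer that T0 pain must be among the strongest predictors of T2 pain and that a large gain is assured. The article gives no correlation and does not support that. At 0.2 or below, the gain is under 2 percentage points.

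A reader might also infer that the data-driven choice of test inflates false positives, or that neither test can give a confidence interval. The simulation does not support the first. The second is wrong: a t-test gives an unadjusted mean difference with an interval, and Wilcoxon can be accompanied by a Hodges-Lehmann shift with one.

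Finally, the tests are introduced as examples, and an article may leave covariates to a fuller plan. This has some force. But the article does fix the form of the primary comparison, and both examples are unadjusted two-sample tests. A better method is available from data already scheduled, so the point goes beyond missing detail.

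**Conclusion.** The concern holds as an efficiency and pre-specification point. The planned primary test is valid, but it discards a pre-treatment measurement of the outcome and the randomisation strata, and it leaves the effect measure undecided.

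The size depends on two quantities that the article does not give. If the standardised difference is 0.44, adjustment raises power from 80% to between 80.4% (correlation 0.1) and 94% (correlation 0.6). The direction is clear, but the magnitude is not established. These figures apply to the score. They do not carry over to a logistic model for prevalence, and the share due to the strata is unknown.

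The article does not support calling the primary analysis biased or its error rate uncontrolled.

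**What to change.** Before any outcome data are seen, name one primary model in the protocol or analysis plan:

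- **For the score:** ANCOVA of T2 maximum pain on arm, T0 maximum pain and the factors used to stratify randomisation, with robust standard errors. Report the adjusted mean difference with 95% CI, and keep Wilcoxon-Mann-Whitney as a sensitivity analysis.
- **For prevalence:** the Study objectives and Sample size sections are framed as prevalence, while the Primary outcome and analysis sections use the score, so the endpoint has to be settled first. If it becomes prevalence, use logistic regression with the same covariates and report a standardised risk difference with 95% CI.
- **Strata:** name the stratification factors.
- **Covariates to avoid or make conditional:** do not adjust for T1 pain, because the experimental arm starts the programme at T0 and T1 is therefore post-intervention. Add planned chemotherapy only if it is recorded before randomisation. Table 1 schedules the risk-factor data at T1 only, and the article does not say that planned chemotherapy is captured at T0.

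The cost is wording. T0 pain is already scheduled and the strata must exist for the randomisation, so no extra patients or visits are needed.

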## Method

### Study design

The APIS trial is a type 1 hybrid randomised controlled trial (RCT), evaluating the effectiveness of the intervention, while also collecting data on key implementation factors in real-world conditions.^16^ This study is designed as an open-label, two-arm, parallel, multicentre, RCT. Patients in the experimental group will begin a personalised APA programme at the start of primary treatment (surgery or neoadjuvant chemotherapy), in parallel with their usual treatment, as illustrated in figure 1. Patients in the control group will receive standard care, with the structured APA programme initiated at the beginning of the AI therapy, namely at the end of primary treatment. In the absence of standardised real-world data on when to initiate APA in postmenopausal women with hormone-sensitive breast cancer, the timing chosen for the control group reflects current local practice. Both groups will have no restrictions on autonomous PA during their care pathway.

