### Study design and assessment time

Figure 3 illustrates the study design aligned with the clinical care pathway, including the timing of randomisation, the APA intervention and data collection time points. Data collection will be structured around standardised key events in the treatment pathway: T0 (during the pre-therapeutic phase), T1 (at the initiation of the AI), T_APA_ (at the end of the 12-week personalised APA programme) and T2 (6 months after the initiation of the AI). The assessment times will be defined by the stages of the care pathway, rather than fixed calendar times, to account for variability in treatment protocols. The interval between T0 and T1 may range from 1 month for patients treated with mastectomy alone, to up to 7 months for those treated with surgery, chemotherapy (with or without targeted therapy) and radiotherapy. The interval between T1 and T2 is fixed at 6 months.

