**Intervention**					
Start of personalised APA protocol, **experimental group**		**X**			
Start of personalised APA protocol, **control group**			**X**		

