#### Follow-up visit at the initiation of AI (T1)

At the start of AI therapy, all patients will undergo a clinical evaluation, functional tests, adverse event monitoring and Self-Report Questionnaires. This visit will occur in the sports medicine department and be conducted by a sports medicine physician.

For the control group, the personalised APA programme will start at this stage.

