#### Follow-up visit at the end of the 12-week personalised APA programme (T_APA_)

T_APA_ will include evaluations similar to those performed at T1.

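### The between-arm comparison at T_APA sets women at different points of aromatase inhibitor exposure and treatment against each other

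*Protocol article*

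**What the plan says.** The Quantitative data analysis section lists, among the analyses of the intervention's effects on secondary outcomes, "between-group comparisons at specific time points (T0, T1, T_APA_, T2". All tests are two-sided at p<0.05.

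The timing of that third visit follows from four other places in the article:

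- **Definition.** Study design and assessment time gives "T_APA_ (at the end of the 12-week personalised APA programme". The visit is tied to programme start.
- **Experimental start.** Under Study design, these women "begin a personalised APA programme at the start of primary treatment (surgery or neoadjuvant chemotherapy". In Table 1 the row "Start of personalised APA protocol" is marked at T0 for this arm. The T0 assessment takes place "before any therapeutic intervention".
- **Control start.** The T1 visit section, at AI initiation, says: "For the control group, the personalised APA programme will start at this stage".
- **Gap between the two starts.** "The interval between T0 and T1 may range from 1 month for patients treated with mastectomy alone, to up to 7 months" with surgery, chemotherapy and radiotherapy.

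The T_APA visit "will include evaluations similar to those performed at T1". Table 1 schedules the self-report questionnaires, walk test, grip strength and anthropometry there. Lung function, exercise testing, Holter monitoring and blood tests are not scheduled at T_APA.

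**The concern.** T1 and T2 are tied to AI initiation in both arms, so they compare like with like. T_APA is tied to programme start, and programme start is exactly what randomisation varies. Randomisation therefore cannot balance AI exposure or treatment stage at T_APA, because the allocated arm fixes the visit date.

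Three kinds of outcome suffer in different ways:

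- **Musculoskeletal pain and endocrine symptoms.** The syndrome under study is caused by AI. Less exposure at the visit makes the experimental arm look better whether or not early exercise works.
- **Fatigue, walk distance and grip strength.** Experimental women on long pathways may still be receiving chemotherapy or radiotherapy. The Background section says muscle deconditioning can appear within weeks of starting chemotherapy, so here the bias can run against the experimental arm.
- **AI adherence.** It cannot be scored in a woman who has not started AI.

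A significant T_APA result could then be reported as a preventive benefit, or as harm, when it reflects only where each arm stood in treatment.

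**Working it through.** **The plan's own figure.** The Sample size section takes 40% against 20%, two-sided 5%, power 80%. With a mean rate of 0.30, n = (1.96·√(2·0.30·0.70) + 0.8416·√(0.40·0.60 + 0.20·0.80))² / 0.20² = (1.270 + 0.532)² / 0.04 ≈ 81.2, so 82 per arm, as stated. This finding does not challenge it; 82 per arm is used below.

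**Step 1: AI exposure at T_APA.** Inputs from the article: programme of 12 weeks; T0–T1 interval L of 1 to 7 months; control start at T1. Conversion: 1 month = 4.35 weeks. Let g be a start lag after T0, in weeks, in the experimental arm only (an assumption; Table 1 implies g = 0).

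- Control: 12 weeks.
- Experimental: max(0, 12 + g − 4.35·L).

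| L (months) | Experimental, g = 0 | Control |
|---|---|---|
| 1 | 12 − 4.35 = 7.65 weeks | 12 weeks |
| 2 | 12 − 8.70 = 3.3 weeks | 12 weeks |
| 3 to 7 | 0 | 12 weeks |

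Exposure reaches zero at L = 12/4.35 = 2.76 months. Beyond that, T_APA comes before T1 in the experimental arm. If the start lag is equal in both arms, experimental T_APA falls 4.35·1 = 4.35 to 4.35·7 = 30.45 weeks earlier, relative to AI start, than control T_APA.

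If L is spread evenly over 1 to 7 months (an assumption), mean experimental exposure is (7.65 + g)² / (2·4.35·6): 1.12 weeks for g = 0, 1.78 for g = 2 and 2.60 for g = 4.

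**Step 2: illustration with no true effect.** Assumptions: pain prevalence stays at a background b until AI starts, then rises linearly to the protocol's 40% at 26 weeks, so prevalence after t weeks of AI is b + (0.40 − b)·t/26. Binary outcome, 82 per arm, two-sided pooled z test at 5%, rejection by exact enumeration. With equal rates this test rejects in 4.9% to 5.0%.

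Worked case, b = 0, even spread, g = 0: control 0.40·12/26 = 18.5%; experimental 0.40·1.12/26 = 1.7%; false difference 16.7 points; rejection 98%.

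| Pathways | Lag g | False difference, b = 30% to b = 0 | Rejection at b = 0 / 10 / 20 / 30% |
|---|---|---|---|
| Even, 1–7 months | 0 | 4.2 to 16.7 points | 98 / 57 / 23 / 9% |
| Even, 1–7 months | 4 weeks | 3.6 to 14.5 points | 87 / 44 / 18 / 8% |
| All 1 month | 0 | 1.7 to 6.7 points | 22 / 12 / 8 / 6% |
| All 1 month | 4 weeks | 0.1 to 0.5 points | about 5% throughout |

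The exposure gap in Step 1 needs no pain model. Step 2 only shows what the gap could do.

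**The case against.** The strongest reply is about weight. This is one interim visit for secondary outcomes; the primary comparison at T2, the comparisons at T0 and T1, and the named T0–T1 and T1–T2 changes are all aligned. That stands, and it limits the finding's scope.

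Second, the sentence is a condensed list in an article, and outcome-by-visit detail is commonly left to an analysis plan. But the complaint is not that detail is missing. The article names T_APA for comparison between arms, and nothing in its text ties T_APA to AI start.

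Third, the article deliberately schedules visits by care-pathway stage rather than calendar. That reasoning protects T1 and T2. T_APA is a programme stage and falls at different pathway stages in the two arms. Asking how women respond to the same 12-week programme during primary treatment or at AI start is a fair descriptive question, and within-arm reporting keeps it.

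Fourth, a start lag narrows the gap: with 4 weeks' lag on a 1-month pathway, exposure is 11.65 against 12 weeks. True, but 12 + g − 4.35·L equals 12 only when g = 4.35·L, that is, when the experimental programme does not start until AI does and the randomised contrast has disappeared.

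Fifth, the rejection rates rest on assumptions. The article gives no pathway distribution and no background pain rate, and Table 2 records pain as intensity and location rather than prevalence. Pain from surgery, chemotherapy or radiotherapy before AI is not modelled and could shrink or reverse the pain difference. This stands for Step 2. It does not alter the exposure gap, and pain from primary treatment would itself be a treatment-stage difference.

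**Conclusion.** The concern holds. By the article's own definitions, the T_APA comparison between arms is confounded with AI exposure and treatment stage. The exposure shortfall in the experimental arm is 4.35 weeks on a 1-month pathway and the full 12 weeks from 2.76 months onward (no lag).

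The resulting bias is less certain than the gap. Under the stated pain model it is small if most pathways are short, background pain is high or the programme starts late, and large if many women have chemotherapy or radiotherapy and background pain is low. For functional outcomes even its direction is open.

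The sentence should be changed, but the primary analysis is untouched.

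**What to change.** In the Quantitative data analysis section, change the list of visits for between-group comparison to T0, T1 and T2. Use T_APA only within each arm, to describe status at the end of the programme. Analyse AI adherence only after AI has started; between arms, that means at T2. This edits one sentence and needs no extra visits, patients or data.

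Optionally, if a comparison about 12 weeks into AI is wanted, add a self-report questionnaire set at T1 + 12 weeks in the experimental arm and compare it with the control T_APA visit. It costs one set for about 182/2 = 91 women, who can enter it themselves on the platform described under Quantitative data management. It would cover questionnaire outcomes only; walk test and grip strength would still be compared at T1 and T2.

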### Intervention

The APA programme, delivered by the sports medicine department, will consist of structured exercises supervised by APA professionals and will be identical for all patients enrolled. The only difference between the two groups is the timing of the intervention within the care pathway: either initiated at the diagnosis of cancer or at the introduction of AI. The APA programme will begin, after a medical evaluation, with a 12-week supervised programme. Each week, the patient will have two 1 hour sessions supervised by a physiotherapist and/or an APA instructor. At the end of the initial 12-week APA programme, the sports medicine physician assesses the patient’s progress and goal attainment to decide whether to renew the programme, refer the patient to a supervised community-based PA, or guide her toward self-directed activity.

After 12 weeks, a new medical consultation will be scheduled, and a new renewal or adjustment phase will begin until the end of the trial.

The detailed APA programme is provided in online supplemental file 1.

In addition to this personalised programme, the interdisciplinary care team will encourage patients to remain physically active throughout the rest of the week, according to their individual abilities. The goal will be for patients to develop specific skills that will support long-term lifestyle changes.

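### Within-arm changes and a between-arm comparison at T0 are listed, at p<0.05, among the analyses of the intervention's secondary effects, although neither estimates the effect of starting APA early

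*Protocol article*

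**What the plan says.** Quantitative data analysis introduces the secondary analyses by their purpose: "Secondary objectives include evaluating the intervention’s effects on outcomes such as physical health, psychosocial well-being and treatment adherence". It then lists three kinds of analysis:

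1. "between-group comparisons at specific time points", with T0 named alongside T1, T_APA and T2.
2. Between-arm comparisons of change, with T0 to T1 and T1 to T2 given as examples.
3. "within-group longitudinal changes across time points".

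One rule covers them all: "All analyses will be two-sided with a significance threshold of p<0.05". The section does not call the T0 comparison or the within-arm analyses descriptive, and it does not say which of the three kinds carries the conclusion.

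Three other places bear on this:

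- The Intervention section says of the programme: "The only difference between the two groups is the timing of the intervention within the care pathway". The T1 visit section has the control arm start it at that visit.
- The T0 section places the baseline examination "before any therapeutic intervention" and randomises patients at that visit.
- Study design and assessment time allows 1 to 7 months of primary treatment between T0 and T1, then a fixed 6 months on the AI to T2.

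**The concern.** The trial question is whether starting APA early does better than starting it when the AI begins. Only a contrast between the randomised arms answers that. Change within one arm combines surgery, any chemotherapy and radiotherapy, the AI, natural course and APA. Because the control arm also receives APA, even a change truly caused by the programme would not show that early start was better.

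The T0 comparison has a different fault. If randomisation is sound, any baseline difference is due to chance, so the test addresses a null hypothesis already known to be true. Its practical risk is that a chance p-value prompts unplanned adjustment.

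What is at stake is the reading of the secondary results. Within-arm p-values appear under the purpose of evaluating effects and share a threshold with the valid contrasts. A report could therefore set a significant change in the experimental arm beside a non-significant one in the control arm and treat the pair as a benefit. That is not a comparison of arms, and its error rate is not 5%.

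**Working it through.** **The plan's own figure.** The Sample size section gives 40% against 20%, two-sided 5%, power 80%, 82 per arm. With pooled variance under the null and no continuity correction:

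n = [1.960·√(2·0.30·0.70) + 0.842·√(0.40·0.60 + 0.20·0.80)]² / (0.40 − 0.20)² = (1.270 + 0.532)² / 0.04 ≈ 81.2, so 82 per arm. Power at 82 is 80.4%.

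For 10% unusable data, 164/0.90 = 182.2, against the stated 182. The figure reproduces, and 82 is used below as the number analysed per arm.

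**Within-arm tests when the arms do not differ.** Let d be the mean change divided by the SD of the change. It is assumed identical in both arms, so the true arm effect is zero. The documents give no expected change, so d is varied.

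- Each arm has a paired t-test with n = 82, 81 degrees of freedom and non-centrality d·√82 = 9.06·d.
- p is the probability that one arm is significant at two-sided 0.05.
- The arms contain different patients, so P(exactly one arm significant) = 2p(1 − p).
- P(only the experimental arm significantly improves) = (probability of significance in the improving direction) × (1 − p).

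| d | p, one arm | Exactly one arm significant | Only the experimental arm significantly improves |
|---|---|---|---|
| 0 | 0.050 | 9.5% | 2.4% |
| 0.10 | 0.146 | 25% | 12% |
| 0.20 | 0.432 | 49% | 25% |
| 0.22 | 0.503 | 50% | 25% |
| 0.25 | 0.609 | 48% | 24% |
| 0.30 | 0.766 | 36% | 18% |
| 0.40 | 0.947 | 10% | 5% |
| 0.50 | 0.994 | 1.2% | 0.6% |

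Worked line, d = 0.20: 2 × 0.432 × 0.568 = 0.491.

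The function 2p(1 − p) cannot exceed 0.50, and it reaches that value at p = 0.5, near d = 0.22. A between-arm test with no true difference is significant in favour of the experimental arm 2.5% of the time. At its worst the one-arm-only pattern is therefore about ten times as frequent (25 / 2.5). With no change at all, or with changes of 0.50 SD or more, it is no more frequent than 2.5%.

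**T0 comparison.** Each test has a 5% chance of significance under sound randomisation. For k independent outcomes the chance of at least one is 1 − 0.95^k, for example 40% at k = 10. Both k and independence are assumptions. None of these results would be an effect of treatment, in either direction.

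**The case against.** The section does not plan a misuse. Two of its three kinds of analysis are between-arm, and they come first. The p<0.05 sentence fixes sidedness and a threshold, not how an effect is concluded. For any outcome measured after T0, a between-arm result would be reported alongside the within-arm one. The T0 comparison may be no more than the baseline table. Within-arm change has a proper descriptive use, for instance in the Maintenance row of Table 3. A condensed article can leave to an SAP which analyses are inferential. All of this stands, and it limits the point.

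It does not remove the point. The article goes beyond leaving a detail open: it names these analyses, gives their purpose as evaluating effects, and applies a significance threshold to all of them. An SAP that follows the text would carry them over.

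Four stronger readings are tempting, and the documents do not support them:

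- That significance in one arm only will be counted as benefit. Nothing says so; the probabilities above apply only if someone reads the results that way and disregards the between-arm contrast.
- That the T0 test could create a false benefit. It precedes the intervention and cannot.
- That about half of such comparisons would mislead. That is the maximum over d, and the rate is far lower at both ends of the table.
- That most of the planned secondary tests are uninformative. The article does not list the tests or say how many intervals the within-arm analyses cover, so no such share can be derived.

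**Conclusion.** The point holds in limited form. Within-arm change cannot isolate early from later APA, and the T0 comparison is uninformative, yet both are listed under the evaluation of effects at p<0.05. If within-arm significance were read as an effect, the chance of a one-arm-only result with no true arm difference would run from 9.5% to about 50% and back to 10% as the common change goes from 0 to 0.22 to 0.40 SD. The share favouring the experimental arm would be at most about 25%, against 2.5%. These figures assume 82 analysed per arm, an identical change in both arms, and a d that the documents do not supply.

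The defect is partial, because valid between-arm contrasts are planned as well, and it touches secondary outcomes only. The planned primary comparison is between arms at T2 and is not affected.

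**What to change.** State in the analysis section, and carry into the SAP, that conclusions about secondary effects rest only on between-arm differences with 95% CIs. Take them at the post-baseline visits where the outcome is measured, T1 and/or T2, and adjust for the T0 value where one exists. T_APA is a poor anchor for this, because the 12 weeks run from T0 in one arm and from T1 in the other, so it falls at different points of the care pathway.

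One model will not fit every outcome:

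- Cardiopulmonary exercise testing and Holter recording are scheduled in Table 1 at T0 and T2 only, so they give one contrast, at T2, adjusted for T0.
- AI adherence has no usable T0 value, since the drug starts at T1. Compare the arms without T0 adjustment.
- Outcomes measured at T0, T1 and T2 can give both contrasts, adjusted for T0.

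Present T0 values by arm, and within-arm changes as means with CIs, descriptively and without p-values. Add one sentence saying that no effectiveness claim rests on them.

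The cost is wording. It needs no extra patients, visits or data, and fewer tests are run. The small downside is that within-arm p-values are no longer reported.
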